**Methods/design:**

In this randomized, single-center, non-inferiority trial, we aim to test the hypothesis that there is no significant difference in cumulative ongoing pregnancy rates between PCOS patients stimulated with LH-based flexible protocol versus traditional flexible GnRH antagonist protocol. The primary efficacy endpoint will be the cumulative ongoing pregnancy rate per cycle. The secondary outcomes will be clinical pregnancy rate, cancelation rate, serious OHSS rate, and cost-efficiency. The cumulative ongoing pregnancy rate per cycle in PCOS women was 80%. Considering that a non-inferiority threshold should retain 80% of the clinical effect of a control treatment, a minimal clinical difference of 16% (two-sided: *α*, 2.5%; *β*, 20%) and a total of 196 patients were needed. Anticipating a 10% dropout rate, the total number of patients required was 216.

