### Sample size calculation

According to the literature and data from our center, the cumulative ongoing pregnancy rate per cycle in women with PCOS in the control arm was around 80%. Considering that a non-inferiority threshold should retain 80% of the clinical effect of a control treatment, a minimum clinical difference of 16% (two-sided: *α*, 2.5%; *β*, 20%) and a total of 196 patients were needed. Considering a possible withdrawal rate of 10%, the total number of patients required will be 216.

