### Statistical analysis

Data analysis of this trial will follow the intention-to-treat principle, including a preliminary comparison of all randomized women in the two groups who did not drop out of the study. Differences between the groups will be compared between demographic variables and baseline information from before the start of the study. Continuous data with normal distribution will be estimated using a two-sample *t*-test, and the Mann-Whitney *U* test will be used for non-normally distributed data. Categorical data will be represented as frequency and percentage, and the differences in these variables will be assessed by the chi-square test or Fisher’s exact test. We will also compute the unadjusted risk ratio (RR) and its 95% confidence interval (CI). This test for non-inferiority will only be performed for the primary outcome; all other secondary outcomes will be tests of superiority. The primary outcome—cumulative ongoing pregnancy rate per cycle in women with PCOS in the control arm—was 80% in our center. Considering that a non-inferiority threshold should retain 80% of the clinical effect of a control treatment, the minimum clinical difference should be 16%. Noninferiority is declared if the upper limit of the two-sided 95% CI for the cumulative ongoing pregnancy rate in the study group does not exceed a relative margin of 16%, equivalent to a two-sided test with an *α* value of 2.5%. A two-sided *α* value of 0.05 is used for superiority testing.

In case of missing values of baseline characteristics, we will analyze them by excluding the missing values, then assign the missing values multiple times, and conduct subsequent analyses to estimate the robustness of the results. For follow-up loss and protocol violation, we will attempt sensitivity analysis to explore the influence of these factors on the trial results.

The flow chart of this study is given in Fig. 1. A schedule of enrollment, interventions, and assessment is provided in the Standard Protocol Items: Recommendations for Interventional Trials (SPIRIT) figure (Fig. 2), and the SPIRIT reporting guidelines are used as shown in Additional file 1 [14].

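### The non-inferiority alpha is labelled two-sided 2.5%, but the 95% CI rule and the 196 patients both correspond to one-sided 2.5%

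*Protocol article*

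**What the plan says.** The error rate of the non-inferiority test appears in three places in the protocol article.

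- Sample size calculation: the parameters are given as "two-sided: *α*, 2.5%; *β*, 20%) and a total of 196 patients were needed". The Methods/design part of the abstract gives the same alpha, beta and total.
- Statistical analysis, decision rule: "Noninferiority is declared if the upper limit of the two-sided 95% CI for the cumulative ongoing pregnancy rate in the study group" stays within a margin of 16%. The same sentence describes this rule as "equivalent to a two-sided test with an *α* value of 2.5"%.
- Statistical analysis, next sentence: superiority tests use a two-sided alpha of 0.05.

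For withdrawals, the sample size section adds: "Considering a possible withdrawal rate of 10%, the total number of patients required will be 216".

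**The concern.** A two-sided 95% CI leaves 2.5% in each tail. A decision that looks at one limit only is a one-sided test at 2.5%. A two-sided test at 2.5% leaves 1.25% in each tail and goes with a 97.5% CI. The sentence that equates the two is therefore wrong as written, and the label in the abstract and the sample size section repeats the error.

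This is the error rate of the trial's only non-inferiority test, on its primary outcome. For a result close to the margin, a 95% and a 97.5% interval can lead to opposite conclusions, and the text as it stands gives some support to each. The Trial status section reports that enrolment was still ongoing, with more than 180 women enrolled, so the wording could be settled before results were known. A correction made afterwards could look like a choice of the more favourable reading.

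**Working it through.** **Inputs**

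- Control rate 80%. Sample size calculation: "the cumulative ongoing pregnancy rate per cycle in women with PCOS in the control arm was around 80"%.
- Experimental rate 80%. This is an assumption (true difference zero). No other value is given, and the abstract's aim is stated as "we aim to test the hypothesis that there is no significant difference in cumulative ongoing pregnancy rates".
- Margin 16 percentage points, taken as an absolute difference. Sample size calculation: "Considering that a non-inferiority threshold should retain 80% of the clinical effect of a control treatment, a minimum clinical difference of 16"%, which is 20% of 80%.
- Power 80% (beta 20%), allocation 1:1.

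**Formula.** Per arm, n = (z_α + z_0.80)² × [0.8 × 0.2 + 0.8 × 0.2] / 0.16² = (z_α + 0.842)² × 0.32 / 0.0256 = (z_α + 0.842)² × 12.5, where z_α belongs to the tail area used at the one limit that is read.

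**Reproducing the plan's figure, one-sided 2.5% (z = 1.960).** n = (1.960 + 0.842)² × 12.5 = 98.1 per arm. Rounded to the nearest whole number this is 98 per arm, or 196 in total, as stated (198 if rounded up).

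**The label taken literally, two-sided 2.5% (1.25% per tail, z = 2.241).** n = (2.241 + 0.842)² × 12.5 = 118.8 per arm, so 119 per arm and 238 evaluable women. This does not give 196.

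**Power**, as Φ(0.16 / √(0.32/n) − z_α):

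| Evaluable per arm | 95% CI, one limit (z = 1.960) | 97.5% CI, one limit (z = 2.241) |
|---|---|---|
| 97 | 79.6% | 70.7% |
| 98 | 80.0% | 71.2% |
| 108 (all 216) | 83.6% | 75.7% |

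For 98 per arm, √(0.32/98) = 0.05714 and 0.16/0.05714 = 2.800. Then Φ(2.800 − 1.960) = 0.800 and Φ(2.800 − 2.241) = 0.712. A Farrington–Manning calculation at 98 per arm gives 78.9% and 69.7%, so the picture does not depend on the variance formula.

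**Other routes to a total near 196**

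- Risk-ratio scale, margin 0.80, two-sided 2.5%: n = 2 × (0.2/0.8) × (2.241 + 0.842)² / (ln 0.80)² = 0.5 × 9.505 / 0.0498 = 95.4 per arm, so 96 per arm and 192 in total. Power at 98 per arm is Φ(0.2231/√(0.5/98) − 2.241) = 81%.
- Ordinary comparison of 80% with 64% at one-sided 5%: 97 per arm, 194 in total.

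Both come close, but the absolute-difference formula at one-sided 2.5% fits best.

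**Withdrawals.** 196 × 1.1 = 215.6, which gives the stated 216. A 10% loss from 216 leaves 216 × 0.9 = 194.4, about 97 per arm, with 79.6% power under the 95% CI rule. Dividing instead, 196/0.9 = 217.8, or 218.

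**The case against.** The best defence is that the rule an analyst would actually apply is clear. The Statistical analysis section names a two-sided 95% CI, and a 97.5% CI is mentioned nowhere. In the abstract and the sample size section, the label can be read as loose shorthand for 2.5% on each side, which fits a 95% CI. This stands in large part: it makes misuse less likely and places the defect in the wording. It does not rescue the decision-rule sentence, which speaks of a two-sided test and is followed at once by a two-sided 0.05 for superiority, where the term has its ordinary meaning.

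A reader might infer that the trial is underpowered, with 71% in place of 80%. The document does not support that. The 71% describes an analysis with a 97.5% CI, which the plan does not specify, and it also requires an absolute margin. On the risk-ratio scale with margin 0.80, even the literal label gives 81% at 98 per arm. The Statistical analysis section calls the margin relative and reports a risk ratio, so that scale cannot be ruled out from the text. For the same reason it would be too strong to say that 196 can be obtained only from one-sided 2.5%. None of the alternatives removes the conflict between a 95% CI and a two-sided 2.5% test.

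The withdrawal arithmetic might be read as a second sample size error of substance. It is a matter of two women (216 against 218) and about 0.4 points of power, which is little beside a control rate given only as approximate.

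**Conclusion.** The point holds as a wrong label and a false equivalence, repeated in three places, on the error rate of the primary test. The 95% CI rule and the total of 196 agree with each other at one-sided 2.5% and give 80.0% power. The stated two-sided 2.5% agrees with neither on the absolute scale. No shortfall in sample size is shown.

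This rests on equal true rates of 80% and an absolute margin of 16 points. The figure of about 71% is conditional on applying the label literally with a 97.5% CI and on that absolute margin. The withdrawal inflation is a side note: about 194 evaluable women and 79.6% power after a 10% loss.

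Two neighbouring matters in the same sentence, the use of the upper limit for a success rate and the description of the margin as relative, are separate and need to be reconciled on their own. The conclusion on the label does not depend on how they are resolved, because reading either limit of a two-sided 95% CI alone is a one-sided 2.5% test.

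**What to change.** In the abstract, the sample size section and the Statistical analysis section, replace the two-sided 2.5% wording with: one-sided alpha 2.5%, assessed with one limit of the two-sided 95% CI, power 80%. Remove the statement of equivalence to a two-sided 2.5% test. Leave the CI level unchanged.

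As a minor addition, keep 216 randomised and state that a 10% loss leaves about 194 evaluable women with about 79.6% power.

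The cost is a text correction, with no additional patients and no change to the 95% CI. The stated power becomes very slightly less favourable (79.6% against 80%).

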**Fig. 1 Fig1:**
[figure not shown]
Flowchart per the checklist of Standard Protocol Items: Recommendations for Interventional Trials (SPIRIT) showing patient enrollment, allocation, treatment, and follow-up of participants

**Fig. 2 Fig2:**
[figure not shown]
SPIRIT figure: the schedule of enrollment, interventions, and assessments

## Discussion

PCOS is a common reproductive endocrine disorder frequently associated with elevated endogenous LH secretion; however, the effects of LH are unpredictable. A study showed that the elevated basal day 2/3 LH levels and LH/FSH ratio do not impair the outcome of GnRH antagonist protocol-treated IVF/ICSI cycles in patients with PCOS [15], which illustrates that suppressing LH values before IVF is not clinically worthwhile for individual patient management. On the other hand, endogenous LH levels are not enough to fully support the development of follicles in some patients. This viewpoint is increasingly being adopted globally. In addition, previous studies indicated that profound LH suppression is detrimental for patients undergoing either GnRH agonist- or GnRH antagonist-treated cycles [16, 17]. The role of LH in PCOS has not been fully studied and seems to be exaggerated without adequate evidence.

Our retrospective cohort study showed that LH could be used as an indicator for the timing and dose of antagonist administration in the GnRH antagonist protocol [11]. We hope that the result will be applicable to a wider population, such as PCOS patients. The trial has a randomized, controlled design which should minimize bias. Data are being collected from a single study center with all investigators required to undertake mandatory training in the protocol, limiting the generalizability of the results. There are also some limitations: the study population is from China and further studies are necessary to verify our conclusions in other ethnic populations, given the genotype and phenotype variations of different ethnic groups. We believe that this proposed trial is unique in that it explores broader considerations, including both the effectiveness, safety, and cost of drugs.

## Trial status

The study was conceived and designed in 2017. Enrollment began in 2018 and is expected to end in December 2022. At the time of manuscript preparation, more than 180 subjects have been enrolled. Enrollment in this study was ongoing at the time of manuscript submission.

## Data Availability

The datasets generated during the current study are available from the corresponding author on reasonable request.

## Abbreviations

AFC: Antral follicle count
AMH: Anti-Müllerian hormone
ART: Assisted reproductive technology
BMI: Body mass index
DMC: Data Monitoring Committee
E2: Estradiol
eCRF: Electronic case report form
ET: Embryo transfer
FSH: Follicle-stimulating hormone
GCP: Good Clinical Practice
Gn: Gonadotropin
GnRH: Gonadotropin-releasing hormone
hCG: Human chorionic gonadotropin
ICSI: Intracytoplasmic sperm injection
IVF: In vitro fertilization
OHSS: Ovarian hyperstimulation syndrome
P: Progesterone
RCT: Randomized controlled trial
SAE: Serious adverse event
SPIRIT: Standard Protocol Items: Recommendations for Interventional Trials
